#### Sample size and data analysis

##### Sample size

The sample size required to estimate the ROC area within 1.5% (based on a 95% confidence interval), assuming an anticipated sensitivity of 90% and specificity of 60%, and assuming 11% of those screened will have COPD is 9669 participants [2, 29]. To ensure an adequate sample size is subsequently available for GECo2, we will recruit a total of up to 10,500 subjects (3500 at each site).

##### Analysis

By site and overall we will summarise the characteristics of those consenting to the study including demographics, exposure history to tobacco and/or household air pollution, anthropometric measurements, spirometry measurements (FEV_1_, FVC and FEV_1_/FVC ratio) and lung function scores (mLFQ, Capture, mMRC dyspnoea scores).

Using a receiver operating characteristic (ROC) area analysis, we will examine the diagnostic accuracy of the questionnaire scores in identifying cases of COPD (compared to spirometry). Curves will be obtained for the mLFQ and CAPTURE questionnaires alone and then each with addition of the PEF scores. Logistic regression models will be used to obtain the ROC curve and area (AUC), with 95% confidence interval. Estimates will be weighted based on census information from each site to better reflect the population. A comparison between the ROC areas will be made by site.

#### Self-management trial (GeCo2)

We invite participants with grades B–D COPD from the case-finding phase to participate in the randomised controlled trial in which they will be randomised to either a multi-faceted intervention to promote adoption of self-management of COPD exacerbations or continue to follow usual care practices for COPD management. Full study information will be provided and all patients will provide written informed consent.

#### Randomisation

Once a participant is determined to be eligible and agrees to enter the study, they will be randomised using an online system (https://www.sealedenvelope.com/) at each local site by the site-specific research team. The computerised randomisation system will use 1:1 allocation to the enhanced support and usual care groups, stratified by country and using random permuted blocks of variable sizes. The assignment allocated to each participant will be recorded in REDCap at local sites by the local research team.

#### Blinding

Principal investigators and members of the data coordinating centre will be blinded to treatment allocation.

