### Follow-up data collection

Data will collected by field workers at baseline and at the 3-, 6-, 9- and 12-month follow-ups (from baseline) (Fig. 5). The baseline data is as collected at the GECo1 visit. It is important to note that the 3-monthly visits from the research staff are not the same as the monthly CHW visits in the intervention arm.

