#### *St. George’s Respiratory Questionnaire (SGRQ)* (primary outcome)

The primary outcome of the trial will be a comparison of the change in SGRQ from baseline to 12 months between the two arms [33]. We will assess respiratory symptoms at baseline, 3, 6, 9 and 12 months post randomisation using the SGRQ. The SGRQ measures impaired health and perceived well-being among individuals with chronic airway disease and offers many advantages for our study, namely: (1) can be used to quantify changes in health following treatment, (2) it is not limited to individuals with COPD and (3) it provides a standard metric that can be used for easy comparison across our three diverse settings [33, 34].

The EuroQol-5D (EQ-5D) questionnaire will be collected at baseline and quarterly through the trial period. The EQ-5D is a generic instrument for describing and valuing health. It is based on a descriptive system that defines health in five dimensions: Mobility, Self-Care, Usual Activities, Pain/Discomfort and Anxiety/Depression [35]. Each dimension has three response categories corresponding to no problems, some problems and extreme problems. The instrument is designed for self-completion, and respondents also rate their overall health on the day of the interview from a 0–100 hash-marked, visual analogue scale (EQ-VAS). Quality-adjusted life years (QALYs) will be derived from the EQ-5D. The EQ-5D has been widely tested and used in both general populations and patient samples and has been locally validated in Nepal, Peru and Uganda [35].

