##### Medication use

We will record pill counts of antibiotics and steroids at quarterly follow-up visits and ask about self-reported frequency and duration of respiratory medications.

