### Implementation outcomes

#### Acceptability

We will conduct key informant in-depth interviews to evaluate acceptability of the intervention from the perspectives of local community members, CHWs, local healthcare professionals, and Ministries of Health over the course of the trial. We will also ask individuals with COPD to evaluate satisfaction with individual components of the intervention in improving quality of life and ability to manage their COPD quarterly.

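### The Blinding section leaves out the field workers who collect the follow-up data, although the primary outcome (SGRQ) is subjective and some of the trial's own procedures may let them learn or guess the arm

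*Protocol article*

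**What the plan says.** The Blinding section reads, in full: "Principal investigators and members of the data coordinating centre will be blinded to treatment allocation".

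Outcome collection is described under Follow-up data collection: "Data will collected by field workers at baseline and at the 3-, 6-, 9- and 12-month follow-ups". The same section adds that "the 3-monthly visits from the research staff are not the same as the monthly CHW visits in the intervention arm", and that the baseline data are those taken at the GECo1 visit.

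The primary outcome section states: "The primary outcome of the trial will be a comparison of the change in SGRQ from baseline to 12 months between the two arms". It describes the instrument as follows: "The SGRQ measures impaired health and perceived well-being among individuals with chronic airway disease". QALYs are to be derived from the EQ-5D.

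Three other places bear on what a field worker could learn about the arm:
- Randomisation: the site team uses the online system, and "The assignment allocated to each participant will be recorded in REDCap at local sites by the local research team".
- Medication use: "We will record pill counts of antibiotics and steroids at quarterly follow-up visits".
- Acceptability: people with COPD are asked each quarter about "satisfaction with individual components of the intervention".

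The section on rescue packs says that health workers give packs to intervention participants from the start of the trial. Controls obtain free packs from a pharmacy or are reimbursed for what they buy.

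**The concern.** Participants know whether they have an Action Plan and monthly visits, so their own reporting cannot be blinded. The conduct of the person who takes the SGRQ is the main remaining point where measurement bias can be limited. The article says who is blinded, and the list omits the staff closest to the primary outcome.

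Baseline is measured before randomisation. Any influence of a field worker who knows the arm would therefore enter only after allocation, and the planned adjustment for baseline SGRQ could not remove it. A larger sample would not remove a systematic shift either.

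At stake is the estimated SGRQ difference, which the GECo2 sample size section says will inform a decision on continuing to a main trial. The QALY-based cost-effectiveness result is also exposed, though less clearly, because the EQ-5D is described as designed for self-completion.

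**Working it through.** **1. Who is blinded and who collects the data**

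| Role | Collects follow-up outcomes? | Listed as blinded? |
|---|---|---|
| Principal investigators | Not stated | Yes |
| Data coordinating centre | Not stated | Yes |
| Field workers | Yes (Follow-up data collection) | No |
| Community health workers | No; their visits are separate | Not applicable, since they deliver the intervention |

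**2. Routes by which the arm may become known**

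- *REDCap.* The local research team records the arm there. Field workers enter data into REDCap, but this is stated only for GECo1.
- *Pill counts.* These are taken at the quarterly visits. Only intervention participants receive packs from a health worker at the start, but controls may hold packs too. A count is suggestive, not decisive.
- *Satisfaction items.* These are asked quarterly. The article does not say who asks them, and one component, education, goes to both arms.
- *Fidelity work.* Study team members observe health worker visits (Fidelity), and quarterly fidelity assessments take place during those visits (CHW-delivered COPD education). The article does not say whether these staff also assess outcomes.

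Keeping research visits apart from health worker visits separates the roles. It closes none of these routes.

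**3. The plan's own figure**

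Inputs from the GECo2 sample size section: SD 25, important difference 4, one-sided 80% interval (z = 0.8416), true difference 0. Allocation is 1:1 (Randomisation).

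n per arm = 2 × (25 × 0.8416 / 4)² = 55.3, rounded up to 56, so 112 in total. This reproduces the stated 112.

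**4. Illustration of what a shift would do at the planned size**

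With N = 240 and no baseline adjustment, SE = 25 × √(4/240) = 3.23, and the one-sided half-width is 0.8416 × 3.23 = 2.72 points.

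Let b be an assumed systematic shift towards the intervention, with a true effect of zero, and let Φ be the standard normal distribution function.

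- Interval fails to exclude a 4-point benefit (the sample size section's criterion): Φ((b − 4)/3.23 + 0.8416)
- Bound on benefit lies above zero (not a criterion in the article): Φ(b/3.23 − 0.8416)

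| Assumed b (points) | Fails to exclude 4 | Bound above 0 |
|---|---|---|
| 0 | 34.5% | 20.0% |
| 1 | 46.5% | 29.7% |
| 2 | 58.8% | 41.2% |
| 3 | 70.3% | 53.5% |
| 4 | 80.0% | 65.5% |

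**5. Effect of baseline adjustment**

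The analysis adjusts for baseline SGRQ. With an assumed baseline correlation of 0.7, SE = 3.23 × √(1 − 0.49) = 2.31. A 2-point shift then moves the first probability from 18.6% to 49.0% and the second from 20.0% to 51.0%. Greater precision makes the result more sensitive to a fixed bias.

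**The case against.** Four objections deserve weight.

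*Silence is not a statement.* The article lists who is blinded; it does not say that field workers are unblinded. A condensed article may leave REDCap user roles and form order to a full protocol or field manual. This stands as a limit: a reader might infer that field workers are known to be unblinded, and the text does not say so. However, the article does have a Blinding section that names the parties, and leaving the outcome collectors off that list is a feature of the text itself.

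*The visit does not necessarily reveal the arm.* A reader might infer that the quarterly visit discloses allocation. The documents do not support that. Controls can hold rescue medicines, pill counts are not restricted to one arm, and nobody is named as asking the satisfaction items. The supportable statement is that these items may suggest the arm.

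*The mechanism is partly inferred.* That field workers administer the SGRQ follows from their role in follow-up and from the Fig. 5 caption, which speaks of the questionnaire being administered. The mode of completion is not stated. If participants complete it alone, interviewer influence is smaller.

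*The magnitude is assumed.* The size and direction of the shift have no source in the documents, and excluding zero is not a stated decision rule. The criterion closest to the text is the interval's position relative to 4 points. A reader might take 20% to 41% as the trial's false-positive risk, but the article sets no such rule.

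The separation of research visits from health worker visits is a real partial safeguard and should be credited. It does not conceal allocation.

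**Conclusion.** The concern holds in a limited form. Followed as written, the plan blinds people who are not described as collecting outcomes and leaves out those who are, for a subjective primary outcome. This leaves an avoidable route for assessment bias after randomisation. It is not evidence that such bias will occur.

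For scale, an assumed 2-point shift (half the important difference) takes the chance of failing to exclude a 4-point benefit from 35% to 59% when there is no true effect. This rests on N = 240 with complete data, SD 25, no baseline adjustment, a normal approximation and a bias favouring the intervention. Blinding the assessors would not remove participants' own reporting bias. The point changes no sample size, and it merits a change to the plan because the remedy is cheap.

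**What to change.** In the Blinding section, add the field workers who administer the SGRQ and EQ-5D to those kept blinded as far as possible. Then, with existing staff:

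- Hide the allocation field and the health worker logs from these field workers' REDCap role.
- Keep them out of randomisation, fidelity observation and health worker supervision for the participants they assess.
- At every follow-up visit, complete the SGRQ and EQ-5D before the pill count, rescue-pack and satisfaction items.
- Where staffing allows, have the 12-month SGRQ taken by an existing field worker who did not do that participant's earlier pill counts or satisfaction items. Form order alone does not protect month 12 if the same person learned the arm at an earlier visit.
- Record whether allocation was disclosed before the SGRQ.
- State that participants' own reporting bias remains. If assessor blinding is not feasible at a site, state that as a limitation.

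The cost is REDCap permissions, form order, a line in field-worker training and slightly less flexible local staffing. No additional assessors are needed.

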#### Intervention arm

The intervention arm will receive (1) basic COPD education, (2) CHW-delivered training in self-management using a locally adapted Action Plan, (3) free CHW-delivered rescue pack medications (steroid, antibiotic) for acute exacerbations (as compared to free rescue medications from local health facilities in the control group). In addition, the intervention arm will receive (4) monthly home visits and (5) continuous access to a CHW with expertise in educating, advising and reinforcing self-management behaviours. (Table 1).

**Table 1 Tab1:** Multi-component strategy for self-directed management of chronic obstructive pulmonary disease (COPD) exacerbations

Component	Description
COPD education (control and intervention arms)	Basic COPD-specific education on (1) risk factors (e.g. household air pollution and tobacco), (2) symptoms and disease progression and (3) how to avoid exacerbations and maintain general lung health (exposure reduction, exercise, sleep and nutrition) using modified versions of standardised educational tools (e.g. ‘flip charts’) administered by trained CHWs
Facilitated self-management Action Plan	2-page Action Plans which colour-code states of respiratory health into green, yellow and red zones. (1) The green zone describes the patient’s baseline respiratory symptoms and actions emphasise daily healthy behaviour and harm reduction strategies, (2) The yellow zone denotes worsening dyspnoea and signifies an exacerbation warranting use of inhaled bronchodilators and orally administered corticosteroids. If there is a change in sputum quantity or colour the addition of antibiotics to corticosteroids is suggested, (3) The red zone pertains to profound dyspnoea or associated symptoms including chest pain, fevers, haemoptysis or change in mentation and urgent medical advice is recommended. Action plans will be facilitated by contact with assigned community health workers
Monthly visitation by CHWs	CHWs will reinforce concepts from the initial COPD education and the Action Plan during monthly visits. CHWs will assess the individual’s ability to recognise symptoms and take appropriate action as indicated by the Action Plan and will be trained to provide feedback and reinforcement accordingly. CHWs will provide additional rescue packs to participants as needed

*CHW* community health worker

#### Control arm

The control arm will receive (1) basic COPD education (see ‘Additional file 1’), (2) access to free medications (steroids, antibiotics) for acute exacerbations available at a local health facility and (3) access to usual care in the local setting. Usual care is as follows per local practice:

##### Nepal

Participants with grades B–D COPD will be referred to the local health centres in their respective catchment areas. They will have access to their local CHW per usual care, though this CHW would not have had extra training or materials pertaining to self-management Action Plans. If indicated by their healthcare provider, medications will be provided by the study team for COPD exacerbation from the Khwopa Public Health Care Centre, our study site.

##### Peru

Participants identified with grades B–D COPD from the case-finding phase (GECo1) will be referred to local health centres in their respective catchment areas. If indicated by their healthcare provider, medications will be provided by the study team for COPD exacerbations.

##### Uganda

Participants with grades B–D COPD will have access to their local CHW per usual care, though this CHW would not have had extra training or materials pertaining to self-management Action Plans. Participants will be referred to local health centres in their respective catchment areas. If indicated by their healthcare provider, medications will be provided by the study team for COPD exacerbation.

#### Formative phase

The intervention strategy was informed by the results of formative research efforts conducted between July 2016 and October 2017. Formative research efforts included in-depth interviews carried out among community participants with COPD, CHWs and healthcare providers/Ministry of Health officials across the three field sites. As part of these efforts, we explored local terminology, perceptions and explanatory models among community members and healthcare practitioners, characterised the supervisory and incentive structures of CHW networks to determine feasibility of a CHW-delivered intervention strategy in each setting, identified, categorised and prioritised multi-level barriers and facilitators to target using the COM-B/Behaviour Change Wheel framework [30]. We then selected intervention functions and behaviour change techniques that targeted the key barriers to adoption to arrive at our final intervention strategy.

#### Intervention design

This CHW-based intervention strategy centred on delivery of locally adapted self-management Action Plans was designed to promote adoption of basic self-management practices and health-seeking behaviours during an acute exacerbation among individuals with COPD. Specifically, the intervention is targeted toward modification of the following health behaviours: (1) monitoring and recognition of warnings signs of a COPD exacerbation and (2) taking prescribed rescue medications and/or seeks attention at a health facility as indicated by evidence-based guidelines.

#### Intervention components

##### CHW-delivered COPD education

All individuals enrolled in the self-management trial (GECo2) (control and intervention) will receive basic COPD education delivered by local CHWs. CHWs will provide COPD-specific education on risk factors (e.g. household air pollution and tobacco), symptoms and disease progression. Additionally, they will be advised on how to avoid exacerbations and maintain general lung health (exposure reduction, exercise, sleep and nutrition). We will use modified versions of standardised educational tools (e.g. ‘flip charts’), which have been previously developed and evaluated in Uganda [31]. Over the course of the trial we will assess the delivery of the health intervention through quarterly fidelity assessments which will take place during monthly CHW visits.

##### Self-management Action Plan

We developed the COPD Action Plan based on existing Action Plans from the UK National Health Service and the American Lung Association for use in each of the three country sites [32]. The Action Plan is identical across the sites, apart from use of local language and illustrations. The Action Plan includes instructions for symptom awareness and medication self-management, with recommendations for tobacco cessation and exposure reduction, pulmonary rehabilitation, exercise, nutrition and sleep, and local health centre contact information. Adaptation of the educational tools (e.g. flip charts) and the COPD Action Plan were informed by the results of formative research efforts. We incorporated local terminology and tailored visual representations of COPD risk factors, pathophysiology, and symptoms to local context (Fig. 3). After the creation of an initial prototype, we then solicited feedback about Action Plan content and layout through consultation with local healthcare practitioners and community members across the sites and updated it accordingly.

**Fig. 3 Fig3:**
[figure not shown]
Chronic obstructive pulmonary disease (COPD) self-management Action Plan. Action plans will be distributed to the intervention arm of trial in addition to medication rescue packs. Sections are colour-coded (green – usual care, yellow – COPD exacerbation self-management, red – urgent medical care)

##### Follow-up visits and reinforcement of self-management practices by CHWs

Follow-up visits by CHWs will occur monthly for the intervention arm. During these visits, CHWs will reinforce concepts from the initial COPD education and the Action Plan. CHWs will assess the individual’s ability to recognise symptoms and take appropriate action as indicated by the Action Plan, and will be trained to provide feedback and reinforcement accordingly. Finally, CHWs will assess medication use through self-report instruments and pill counts, and provide additional rescue packs as needed. CHWs will keep detailed records of contacts with participants.

##### Access to CHW-delivered rescue packs for acute exacerbations

Both the intervention and control arms will receive access to rescue medications for COPD. CHWs will deliver rescue packs (prednisone and antibiotics – local choice) to intervention arm participants at the beginning of the trial and as needed (Fig. 4). Control arm participants will receive either free rescue packs from a local pharmacy or be reimbursed for rescue medications purchased during the trial, depending on local norms and requirements. The efficacy of corticosteroids and antibiotics for COPD exacerbations has been previously well documented. We intend to specifically assess the effectiveness of a multi-faceted intervention to promote self-management of COPD exacerbations at a community level. While both study arms will receive medications for management of COPD exacerbations, we hypothesise that a multi-faceted strategy of self-directed care will lead to improved health outcomes and be cost-effective.

**Fig. 4 Fig4:**
[figure not shown]
Rescue pack for chronic obstructive pulmonary disease (COPD) exacerbations. Medications based on GOLD recommendation for treatment of COPD exacerbations and local prescribing practices

#### Role of the CHWs

CHWs will deliver basic COPD education to all individuals who are diagnosed with COPD in the case-finding phase (GECo1). CHWs will additionally support the self-management action plan, of those participants recruited to the self-management trial (GECo2) and randomised to the intervention arm via monthly visits and distribution of rescue packs for COPD when required. The CHWs will have three roles:*Role 1*: relevant during GECo1 and throughout the studyThe CHW will deliver COPD education within 72 h of COPD diagnosis via educational flip-charts. There will be no mention of self-management Action Plans, just basic COPD education delivery via flip charts (see ‘Additional file 1’)*Role 2*: relevant during GECo2The CHWs will be trained by the research team to support the self-management Action Plans. They will be taught how to teach participants to use the Action Plan; symptoms to be mindful of; and to remind participants to partake of daily physical activity, eat well and sleep well. They will also issue participants in the intervention arm a rescue pack of antibiotics and steroids, educate them when and how to take them and reinforce that they are contactable daily for advice regarding COPD and self-management*Role 3*: relevant during GECo2The CHWs will conduct monthly visits to the participants’ homes in the intervention arm (approximately one participant per week per CHW). At each visit they will reiterate the education listed above and re-emphasise the role and use of the Action Plan. They will re-stock medications if a rescue pack has been used. They will record if a pack has been used, when it was used, and whether the medications were initiated correctly and the course was completed. They will record what symptoms the participant experienced that prompted them to take the medications in each instance. Monthly visits by the CHWs to the intervention arm participants to support the Action Plan will occur to aid in promotion of behavioural changes

